### 143 3.2.2 Exclusion criteria

144 1) Participated in any myopia control clinical research trial within 3 months, used or is currently  
145 using multifocal contact lenses, atropine drugs, etc.;

146 2) Children with strabismus and amblyopia;

147 3) Congenital eye diseases, such as congenital cataracts and congenital retinal diseases;

148 4) Secondary myopia (such as secondary myopia caused by retinopathy of prematurity or  
149 other infant eye diseases), or myopia combined with systemic syndromes (such as Marfan  
150 syndrome);

151 5) People who have undergone myopia correction (such as LASIK, etc.), internal eye surgery  
152 (such as cataract extraction, intraocular lens implantation, etc.);

153 6) refractive media turbidity (such as keratopathy, crystal turbidity, etc.)

- 154 7) Abnormal IOP (IOP < 10 mmHg or > 21mmHg or binocular IOP asymmetry  $\geq$ 5mmHg);  
155 8) Patients with fundus retinopathy or other intraocular diseases;  
156 9) Patients with optic nerve damage or congenital optic nerve dysfunction;  
157 10) Have systemic diseases that may affect the eyes, such as diabetes, Down syndrome,  
158 hyperthyroidism, etc;  
159 11) Only one eye meets the inclusion criteria;  
160 12) Those who cannot regularly (or the guardian cannot regularly accompany the children)  
161 carry out eye examination;  
162 13) Other reasons that the doctor considers unsuitable for inclusion in the program.

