### 163 **3.2.3 Sample size**

164 The sample size estimation was estimated based on the assumption of a 2-sided  $\alpha$  level of  
165 0.05, 90% power. The axial elongation among Chinese children with premyopia or mild myopia  
166 was approximately 0.40 mm per year (standard deviation [SD]: 0.25 mm) according to the  
167 literature. A 50% treatment effect was expected (reducing axial elongation by 0.20 mm). The  
168 sample size was required 34 per group. A total of at least 85 participants was obtained after  
169 adjusting for a 20% loss to follow-up. The sample size was calculated using PASS 15.0 (NCSS,  
170 Utah).

171

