### 178 **3.4 Study intervention and termination**

179 All intervention patients underwent RLRL therapy using a desktop red light therapy device  
180 (Eyerising, Suzhou Xuanjia Optoelectronics Technology, Jiangsu, China). After device  
181 dispensing, intervention patients were advised to complete treatment twice a day under their  
182 parents' supervision. Each treatment session lasted for 3 minutes, separated by at least 4  
183 hours. In the absence of adverse effects, patients were instructed to repeat the treatment on

184 five days per week. Treatment dates and times were recorded via the internet, allowing  
185 researchers to monitor participant adherence.

186 The power of the semiconductor laser output by this device as the light source for the eyes  
187 is 1.07mW, with a wavelength of 650nm. It has been detected as a Class 1 laser by the National  
188 Quality Supervision and Inspection Center for Photoelectric Product Optical Radiation Safety,  
189 meaning that it is safe for the eyes to be directly irradiated.

190 Model specification of the therapeutic instrument: RS - 200 - 2A

191 (1) Input power  $\leq 100\text{VA}$ , input voltage: AC10V - 240V, 50Hz/60Hz.

192 (2) Wavelength of the low-intensity single-wavelength red light:  $650\text{nm} \pm 10\text{nm}$ .

193 (3) Diameter of the low-intensity single-wavelength red light cursor:  $7\text{mm} \pm 3\text{mm}$ , and  
194 the light spot at the observation port is:  $10\text{mm} \pm 2\text{mm}$ .

195 (4) Light source output power:  $2.0\text{mW} \pm 0.5\text{mW}$ ; at a distance of 100mm from the light  
196 source, it is 1.07 - 1.42mW.

197 The intervention will be terminated when the subject experiences an unexpected serious  
198 adverse reaction (including a sharp decline in vision by more than two lines or a central  
199 scotoma in the visual field), the guardian or the participant requests to withdraw from the  
200 study, or for other reasons.

201

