#### 241 **5. Statistical Analyses**

242 For each subject, data from the right eyes were utilized for analyses. Missing data were not  
243 imputed or replaced. The changes in ocular parameters were calculated as a difference  
244 between baseline and the respective follow-up values.

245 Statistical analysis includes statistical descriptions and statistical inference. Continuous  
246 variables were presented as means and standard deviations, while categorical data were  
247 presented by frequency and percentage. Group differences between the RLRL and control  
248 groups were assessed using t-test or ANOVA for continuous data and the Chi-square test for  
249 categorical data. Statistical significance was set at two-sided  $P < 0.05$ , and all analyses were  
250 performed using SPSS software version 21.0 (IBM., Chicago, IL).  
251

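### The right-eye rule in section 5 makes no exception for myopia incidence or ocular safety, so left-eye-only onset and left-eye changes short of a serious event have no place in the planned comparisons

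*Protocol*

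**What the plan says.** Protocol section 5 opens with the unit of analysis, stating for every child that "data from the right eyes were utilized for analyses". It then defines change from baseline for the ocular parameters and assigns a t-test or ANOVA to continuous data and a chi-square test to categorical data. No outcome is exempted from the right-eye rule.

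Elsewhere the protocol treats the child, or both eyes, as the unit:

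- Section 3.2.2, criterion 11, excludes a child when "Only one eye meets the inclusion criteria", so every enrolled child has two eligible eyes.
- Section 3.4 describes the device with the words "The power of the semiconductor laser output by this device as the light source for the eyes". Exposure of both eyes is implied by the plural but not stated outright.
- Section 3.4 ends the intervention when the subject has a serious "adverse reaction (including a sharp decline in vision by more than two lines or a central" scotoma. It does not restrict this to one eye.
- Section 3.5.2 lists UCVA, BCVA, SER, SFCT, CCT and the myopia incidence rate as secondary outcomes. It does not say whether incidence is counted per eye or per child.
- Section 3.6.1 schedules adverse events at every follow-up visit, and BCVA, slit lamp, IOP, fundus photography and OCT at baseline and every follow-up visit. Section 6 records and reports all serious adverse events. None of this is tied to the right eye.

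**The concern.** A one-eye rule suits a continuous measurement and suits an event poorly. A parent or clinician asks whether the child became myopic or lost vision, and the right eye answers that only in part. Section 5 fixes the rule for every analysis, so it reaches two places where it does damage.

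- **Myopia incidence.** Onset confined to the left eye is classified as no onset. The trial's stated objective is prevention in children at high risk, so this outcome matters.
- **Ocular safety measures.** The project title covers both efficacy and safety. A left-eye fall in BCVA enters no BCVA comparison. A left-eye OCT change that is not a serious adverse event has no stated place in the group comparisons. The rule for ending treatment and the rule for analysis therefore use different units: a child could stop treatment because of left-eye vision while the BCVA analysis shows no change.

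**Working it through.** **1. The plan's own sample size.** Inputs from section 3.2.3: two-sided alpha 0.05, power 90%, control elongation that "was approximately 0.40 mm per year (standard deviation [SD]: 0.25 mm"), and a treatment effect "reducing axial elongation by 0.20 mm". Section 3.3 gives 1:1 allocation. The standardised difference is 0.20/0.25 = 0.8.

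- Noncentral t, two groups: n = 33 gives power 0.8926 and n = 34 gives 0.9015, so 34 per group. This reproduces the plan.
- Loss to follow-up of 20%: 68/0.8 = 85 in total, or 34/0.8 = 42.5, rounded up to 43 per group (86). Both figures in the protocol reproduce.

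The calculation counts children with one value each, which is what a right-eye analysis supplies. The primary analysis and the sample size agree.

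**2. Myopia onset: right eye against either eye.** The protocol gives neither a per-eye incidence nor a between-eye correlation, so both are assumed. Let p be the incidence per eye, equal for the two eyes, and phi the between-eye correlation of onset among children with neither eye myopic at baseline.

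- Both eyes: b = p² + phi·p(1 − p)
- Either eye: 2p − b
- Left eye only, missed by right-eye counting: p − b
- Share of affected children missed: (p − b)/(2p − b)

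Example, p = 0.20 and phi = 0.7: b = 0.04 + 0.7 × 0.16 = 0.152. Either eye = 0.40 − 0.152 = 0.248. Missed = 0.048/0.248 = 19.4%. Incidence is 20.0% by right eye and 24.8% by either eye.

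| p | phi | Either eye | Share missed |
|---|---|---|---|
| 0.10 | 0.5 | 14.5% | 31.0% |
| 0.10 | 0.7 | 12.7% | 21.3% |
| 0.10 | 0.9 | 10.9% | 8.3% |
| 0.20 | 0.5 | 28.0% | 28.6% |
| 0.20 | 0.7 | 24.8% | 19.4% |
| 0.20 | 0.9 | 21.6% | 7.4% |
| 0.30 | 0.5 | 40.5% | 25.9% |
| 0.30 | 0.7 | 36.3% | 17.4% |
| 0.30 | 0.9 | 32.1% | 6.5% |

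**3. Axial length: what the second eye would add.** The mean of two eyes has SD 0.25 × √((1 + rho)/2), where rho is the between-eye correlation of axial-length change. The protocol does not give rho, so it is assumed. Power at 34 per group, noncentral t:

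| rho | SD (mm) | Variance saved, (1 − rho)/2 | Power |
|---|---|---|---|
| right eye only | 0.2500 | – | 90.2% |
| 0.95 | 0.2469 | 2.5% | 90.8% |
| 0.9 | 0.2437 | 5% | 91.5% |
| 0.8 | 0.2372 | 10% | 92.9% |
| 0.7 | 0.2305 | 15% | 94.1% |

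The gain is between 0.6 and 3.9 percentage points of power.

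**The case against.** The strongest reply is that the right-eye sentence leads straight into the definition of change in ocular parameters, and so is naturally read as the unit rule for eye measurements rather than for adverse events. Adverse-event collection, serious-event reporting and the rule for ending treatment are all per subject. Safety tables are commonly left to a statistical analysis plan. The rule also applies alike in both groups, so the right-eye comparison is coherent and no between-group bias has been shown.

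Much of this stands, and it rules out three stronger readings.

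- A reader might infer that left-eye harm is never counted. The protocol does not support that: nothing restricts adverse events, serious adverse events or treatment termination to the right eye.
- A reader might infer that half of all ocular events are missed. That holds only for events strictly confined to one eye and equally likely on either side. Bilateral events are not missed.
- A reader might infer that half the axial-length information is thrown away. Half the measurements are unused, but a child's eyes are correlated. The variance saving is (1 − rho)/2, which reaches 50% only at rho = 0. A fixed, prespecified eye leaves no room for choosing the eye afterwards and does not treat paired eyes as independent.

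The reply does not dispose of the point itself. Section 5 states a rule and gives no exception; it does not leave the matter open. BCVA and myopia incidence are listed outcomes to which the rule applies as written, and serious-event reporting does not pick up left-eye changes that fall short of that threshold.

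**Conclusion.** The point holds in a limited form. Followed literally, section 5 classifies left-eye-only myopia onset as no onset and leaves left-eye BCVA loss or OCT change, when short of a serious adverse event, outside the planned comparisons. For incidence, about 6.5% to 31% of children with onset in either eye would be missed. That range rests on assumed per-eye incidence of 10–30%, assumed phi of 0.5–0.9, and equal incidence in the two eyes. No size can be put on the safety gap, because the protocol gives no event rates and no indication of how often findings would be bilateral.

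The axial-length analysis is not in error. The plan's 34 per group reproduces at 90.2% power, and averaging the eyes would be a modest improvement rather than a correction. The text is worth changing because the remedy is cheap and the affected outcomes bear directly on prevention and safety.

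**What to change.** In section 5:

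1. Limit the right-eye rule to continuous efficacy measures.
2. Define myopia incidence per child, as onset in either eye, among children with neither eye myopic at baseline. The baseline condition is needed because section 3.2.1 admits children with mild myopia as well as pre-myopia.
3. State that BCVA loss and OCT, fundus, slit-lamp and IOP abnormalities are summarised per child using both eyes, with the affected eye listed. Counting an abnormality in either eye avoids a worse-eye rule, which would be ambiguous for IOP because section 3.2.2 treats both low and high values as abnormal.
4. Optionally, analyse axial length and the other continuous outcomes as the mean of the two eyes, with the right eye as a sensitivity analysis, or the reverse. At 34 per group this moves power from 90.2% to about 91–94% for assumed rho of 0.95 to 0.7.

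**Cost.** A few sentences, with no added child or visit. The measurements should already be on file, since both eyes must qualify and section 3.6.2 applies cycloplegic drops to both. The sample size stays as it is. If the two-eye mean becomes primary, comparison with publications that report the right eye alone would use the right-eye results.

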## 139 3.2 Participants

### 140 3.2.1 Inclusion criteria

141 1) Children aged 7-12 years old.

142 2) Children with pre-myopia or mild myopia.

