## 202 **3.5 Outcomes**

### 203 **3.5.1 Primary outcome**

204 The primary outcome is AL change from baseline at 1 year between the two groups.

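### Free improvement: adjust the primary axial length comparison for baseline axial length, age and refractive status, in place of an unadjusted t-test or ANOVA

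*Protocol*

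**What the plan says.** Protocol section 3.5.1 defines the endpoint: "The primary outcome is AL change from baseline at 1 year between the two groups". Section 5 analyses right eyes, takes each change as the difference between baseline and follow-up, does not impute missing values, and then fixes the test: RLRL and control "groups were assessed using t-test or ANOVA for continuous data and the Chi-square test for" categorical data. No ANCOVA, regression or mixed model appears, and no covariate is named.

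Section 3.2.1 admits ages 7 to 12 and "Children with pre-myopia or mild myopia". Section 3.3 describes 1:1 allocation from a computer-based random number table and names no stratification factor. The visit schedule in section 3.6.1 has AL, non-cycloplegic refraction and cycloplegic refraction at baseline. Section 6 adds that children whose anterior chamber angle is very narrow are not given the mydriatic examination.

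Section 3.2.3 sizes the trial on a control elongation that "was approximately 0.40 mm per year (standard deviation [SD]: 0.25 mm) according to the" literature. It then says: "A 50% treatment effect was expected (reducing axial elongation by 0.20 mm"), and "sample size was required 34 per group" before allowance for loss.

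**The concern.** Eligibility spans six years of age and two refractive categories. If age, starting eye length and refractive status predict a year's elongation, two things follow from leaving them out. The variance they explain stays in the error term and widens the interval. And any chance difference between arms in these variables passes into the treatment estimate, because neither the allocation as described nor the analysis deals with it.

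The choice between t-test and ANOVA does not help. With two groups at one time point, a one-way ANOVA gives F = t² and the same P value as the pooled t-test.

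Timing also matters. If an imbalance shows up in the data, an adjustment chosen then is post hoc and open to challenge. Naming the covariates beforehand avoids having to choose between an estimate that carries the imbalance and an unplanned analysis.

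**Working it through.** **Inputs from protocol section 3.2.3:** two-sided α = 0.05, 90% power, difference 0.20 mm, SD 0.25 mm, 34 evaluable per group, 20% loss. **Assumed, because the protocol gives no figure:** R², the share of variance in 12-month AL change explained by the covariates, from 0.05 to 0.30.

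**1. The plan's own figure.** Two-sample t-test with standardised difference 0.20/0.25 = 0.8, using the noncentral t with 2n − 2 degrees of freedom:
- n = 33 per group: power 89.3%
- n = 34 per group: power 90.2%

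So 34 is the smallest adequate number. Allowing for loss, 68/0.8 = 85 in total; rounding up per group, 34/0.8 = 42.5, hence 43 per group and 86 in total. Both of the protocol's totals reproduce. The sample size and the planned unadjusted test agree.

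**2. Precision of the unadjusted analysis.** Half-width = t(0.975, 66) × SD × √(2/n) = 1.997 × 0.25 × √(2/34) = 1.997 × 0.0606 = 0.121 mm.

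**3. Precision with adjustment.** Residual SD = 0.25 × √(1 − R²), same formulas, 34 per group. The last column, 34/(1 − R²), is the unadjusted group size that would give about the same precision.

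| R² (assumed) | Residual SD (mm) | Power for 0.20 mm | 95% CI half-width (mm) | Equivalent n per group |
|---|---|---|---|---|
| 0 (unadjusted) | 0.250 | 90.2% | 0.121 | 34 |
| 0.05 | 0.244 | 91.5% | 0.118 | 35.8 |
| 0.10 | 0.237 | 92.9% | 0.115 | 37.8 |
| 0.20 | 0.224 | 95.3% | 0.108 | 42.5 |
| 0.30 | 0.209 | 97.3% | 0.101 | 48.6 |

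Three covariates take the degrees of freedom from 66 to 63. That costs less than 0.1 percentage point of power in every row.

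**4. Chance imbalance.** With simple 1:1 allocation and 34 per group, the standardised difference in any one covariate has standard deviation √(2/34) = 0.243. The chance that it exceeds 0.3 SD in either direction is 2 × [1 − Φ(0.3/0.243)] = 2 × [1 − Φ(1.237)] ≈ 22%. The resulting shift in the unadjusted estimate is √R² × 0.25 × 0.3, where R² now belongs to that one covariate:
- R² = 0.10: 0.316 × 0.075 = 0.024 mm
- R² = 0.30: 0.548 × 0.075 = 0.041 mm

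Against the expected 0.20 mm, these are 12% and 21%.

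**The case against.** The strongest reply is that nothing here is wrong. Under randomisation an unadjusted t-test on change scores keeps its type I error and is unbiased on average, and its standard error already allows for chance imbalance. The trial is sized for exactly this test, and the assumed SD is quoted for children with premyopia or mild myopia, so the mixed population is already in the calculation. The design half-width of 0.121 mm around 0.20 mm runs from about 0.08 to 0.32 mm and excludes zero. All of this stands, and it is why the point is an improvement and not an error.

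The gain also depends on an assumed R². At 0.05 it is 0.003 mm of half-width and 1.4 points of power (from 90.15% to 91.54%); near zero there is none. That stands too.

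It can be said that covariates belong in the SAP, which is not at hand. This carries less weight: section 5 does not leave the test open. It names one, and that is the text to change.

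Three stronger readings might be inferred, and the protocol supports none of them.
- *That baseline AL is discarded.* It is subtracted in the change score; it is only not used as a covariate.
- *That the trial is underpowered or the test invalid.* Step 1 of the working shows otherwise.
- *That cycloplegic refraction exists for every child and can be added without cost.* Section 6 spares children with a very narrow angle the mydriatic examination, section 3.2.2 does not list them as an exclusion, and section 5 does not impute. A cycloplegic refraction covariate could therefore drop some children from the primary analysis, though probably few.

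Nor does section 3.3 say that allocation was unstratified; it names no factor.

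**Conclusion.** The point holds as a free improvement. Section 5 fixes an unadjusted primary comparison in a population mixed by design, although variables for adjustment are already collected. The test is valid and 34 per group gives 90.2% power for it, so what is at stake is precision and protection against chance imbalance. For assumed R² of 0.05 to 0.30, adjustment brings power to about 91.5% to 97.3% and narrows the half-width to about 0.118 to 0.101 mm. The result rests on the protocol's SD of 0.25 mm, 34 evaluable children per group, and an R² that the protocol does not give.

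**What to change.** Replace the general test sentence in section 5, for the primary outcome, with one named analysis: ANCOVA of 12-month AL change in the right eye on arm, adjusted for baseline AL, age and baseline refractive status (pre-myopia versus mild myopia, as classified at enrolment). Report the adjusted mean difference between arms with its 95% confidence interval, and keep the unadjusted t-test as a supportive analysis.

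Use refractive status as the refraction covariate, not cycloplegic spherical equivalent, so that children who do not have the mydriatic examination stay in the analysis.

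The cost is one paragraph of wording. It needs no extra visits, measurements or participants, and the sample size calculation can stay as it is. The change should be made before the outcome data are seen by arm, since prespecification is what gives it its value.

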## 252    **6. Advent events**

253    The intervention measure in this study is an amblyopia treatment device that has been widely  
254    used and is known to have no side effects. After using the treatment device, there may be  
255    transient reactions such as photophobia, lacrimation, mild stinging, glare, and photosensitivity.  
256    Resting with the eyes closed for a few minutes can help relieve these symptoms  
257    spontaneously. During the cycloplegic examination in the research process, some children  
258    may experience transient discomfort, such as difficulty with near reading and photophobia.  
259    These discomforts will completely disappear within 5 to 72 hours. If photophobia causes  
260    inconvenience during movement, the researchers will provide clip-on sunglasses to alleviate  
261    the discomfort. Some people may experience transient difficulty with near vision,  
262    photophobia, and other discomforts, which will typically disappear within 5 to 72 hours. For  
263    those with photophobia and blurred near vision, this study will provide sunglasses and, if  
264    necessary, reading glasses with near-addition lenses for easy reading.

265       Less than one in a thousand people may experience increased intraocular pressure,  
266    headache, eye pain, and vomiting (manifestations of acute angle-closure glaucoma). All  
267    subjects will be preliminarily screened with a slit lamp. Patients with a very narrow anterior  
268    chamber angle will not undergo mydriatic examination. If a subject experiences symptoms  
269    such as increased intraocular pressure, headache, or eye pain, on-site staff will promptly  
270    provide medical treatment and take referral measures.

271       All serious adverse events will be recorded using the SAE Case report form. Any SAE will be  
272    reported to the investigator and Institutional Ethics Committee.

273

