48    BCVA = best-corrected visual acuity;

49    CCT = central corneal thickness;

50    D = diopter;

51    IOP = intraocular pressure

52    UCVA = uncorrected visual acuity;

53    OCT = optical coherence tomography;

54    RCT = randomized controlled trial;

55    RLRL = repeated low-level red-light;

56    RPE = retinal pigment epithelial;

57    SAE = serious adverse event

58    SFCT = subfoveal choroidal thickness;

59    SER = spherical equivalent refraction;

60

61

62

63    **1. Trial information**

64    **1.1 Title of project**

65    the efficacy and safety in children following 650 nm red-light therapy for myopia control

66

67    **1.2 Trial summary**

68    **Objective:** To observe the effect of low-intensity 650 nm red light on the prevention of  
69                   myopia in adolescents, whether it can effectively curb myopia or slow down the  
70                   development of myopia in children at high risk of myopia. we hope to provide  
71                   new methods and ideas for effectively controlling myopia.

72    **Trial Setting:** The randomized controlled clinical trial is planned to be conducted between  
73                   September 2021 and September 2023 at the Eye Center of the Children's  
74                   hospital of Fudan University, China

75    **Sample size:** A sample size of 86 (43 in each group) is estimated after adjusting for a 20% loss  
76                   to follow-up.

77    **Inclusion criteria:** 1) Children aged 7-12 years old.

78                   2) Children with pre-myopia or mild myopia.

79    **Exclusion criteria:** 1) Participated in any myopia control clinical research trial within 3 months,  
80                   used or is currently using multifocal contact lenses, atropine drugs, etc.;

81                   2) Children with strabismus and amblyopia;

82                   3) Congenital eye diseases, such as congenital cataracts and congenital  
83                   retinal diseases;

84                   4) Secondary myopia (such as secondary myopia caused by retinopathy of  
85                   prematurity or other infant eye diseases), or myopia combined with  
86                   systemic syndromes (such as Marfan syndrome);

87                   5) People who have undergone myopia correction (such as LASIK, etc.),  
88                   internal eye surgery (such as cataract extraction, intraocular lens  
89                   implantation, etc.);

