### 205 **3.5.2 Second outcomes**

206 1) the changes of UCVA and BCVA

207 2) the changes of SER, SFCT and CCT

208 3) the changes in the myopia incidence rate between the two groups.

209

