## 210 **3.6 Study procedures**

### 211 **3.6.1 Study visit schedule**

| Examination                                      | baseline | 1 months | 3 months | 6 months | 9 months | 12 months |
|--------------------------------------------------|----------|----------|----------|----------|----------|-----------|
| Education and machine distribution               | √        | –        | –        | –        | –        | –         |
| Informed consent                                 | √        | –        | –        | –        | –        | –         |
| UCVA                                             | √        | √        | √        | √        | √        | √         |
| BCVA                                             | √        | √        | √        | √        | √        | √         |
| Noncycloplegic refraction (objective/subjective) | √        | √        | √        | √        | √        | √         |
| cycloplegic refraction (objective/subjective)    | √        | –        | –        | √        | –        | √         |
| AL                                               | √        | √        | √        | √        | √        | √         |
| Slit lamp exam                                   | √        | √        | √        | √        | √        | √         |
| Intraocular pressure                             | √        | √        | √        | √        | √        | √         |
| fundus photography                               | √        | √        | √        | √        | √        | √         |
| optical coherence tomography (OCT)               | √        | √        | √        | √        | √        | √         |
| Advent events                                    | –        | √        | √        | √        | √        | √         |
| Machine recovery                                 | –        | –        | –        | –        | –        | √         |

212

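### Section 6 says the device has no side effects and then lists some; the title names safety, but no safety outcome is designated, and the right-eye rule keeps left-eye acuity loss out of BCVA

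*Protocol*

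**What the plan says.** **On known effects.** Protocol section 6 describes the device as widely "used and is known to have no side effects. After using the treatment device, there may be" "transient reactions such as photophobia, lacrimation, mild stinging, glare, and photosensitivity". It adds that these settle with a few minutes' rest.

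**On the trial's scope.** The project title (section 1.1) is "the efficacy and safety in children following 650 nm red-light therapy for myopia control". The objective in section 1.2 and the aim in section 2 speak of efficacy only.

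**On outcomes.** Section 3.5.1: "The primary outcome is AL change from baseline at 1 year between the two groups". The secondary outcomes in section 3.5.2 begin with "the changes of UCVA and BCVA" and go on to SER, SFCT, CCT and myopia incidence. None is labelled a safety outcome, and adverse events are not among them.

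**On analysis.** Section 5 takes right-eye data for every subject and states no exception. It names the Chi-square test for categorical data. Exclusion criterion 11 (section 3.2.2) requires both eyes to be eligible.

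**On collecting harms.** The visit schedule (section 3.6.1) has a row for "Advent events" ticked at 1, 3, 6, 9 and 12 months. BCVA, slit lamp, IOP, fundus photography and OCT are ticked at every visit. Section 3.4 ends treatment for an unexpected serious "adverse reaction (including a sharp decline in vision by more than two lines or a central" scotoma. Section 6 adds: "All serious adverse events will be recorded using the SAE Case report form", with reporting to the investigator and the ethics committee.

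**The concern.** There are three linked points.

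1. A protocol for children aged 7 to 12, which goes to an ethics committee, states that the device has no side effects and then names five reactions to it. Both statements cannot stand.

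2. A trial titled as a study of efficacy and safety should say in advance which result will carry the safety conclusion. Here no outcome does. Choosing outcomes is the protocol's task, and this protocol has a full outcome section, so an analysis plan that is not shown does not fill the gap.

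3. BCVA is the listed outcome nearest to visual harm. Treatment is given to children whose eyes must both be eligible, but under the rule in section 5 a left-eye loss of acuity cannot appear in the BCVA result.

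At stake is what a reader can conclude about harm: no count of harmed children per arm is named before the data are seen.

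**Working it through.** **Step 1. The two statements in section 6.** The first says the device has no side effects. The second lists photophobia, lacrimation, mild stinging, glare and photosensitivity after its use. That the reactions are transient makes them mild, but they are still side effects.

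**Step 2. The title against the outcome list.** Outcomes named in sections 1.2, 3.5.1 and 3.5.2: AL, UCVA, BCVA, SER, SFCT, CCT and myopia incidence. Labelled as safety: none. Adverse-event outcomes: none.

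**Step 3. The arm size, reproduced.** Section 3.2.3 requires 34 per group before a 20% loss: 34 / (1 − 0.20) = 42.5, so 43 per arm. This agrees with section 1.2. The figures below use 43.

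**Step 4. What the right-eye rule would cost a count of acuity loss.** The protocol gives no rate for such loss. Assume that a fraction p of treated children lose vision in one eye, with either eye equally likely. The chance that at least one case appears among 43 children is 1 − (1 − p)^43 if either eye counts, and 1 − (1 − p/2)^43 if only the right eye counts.

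| p (assumed) | Either eye | Right eye only |
|---|---|---|
| 1% | 35% | 19% |
| 2% | 58% | 35% |
| 5% | 89% | 66% |

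For p = 2%: 1 − 0.98^43 = 0.58 and 1 − 0.99^43 = 0.35. This concerns only an acuity result built from right-eye data. It does not apply to adverse-event recording, which section 3.6.1 does not limit to one eye.

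**Step 5. How precise a per-child count would be.** One affected child in an arm is 1/43 = 2.3%. The lower exact (Clopper-Pearson) 95% limit is 1 − 0.975^(1/43) = 0.06%, and the upper limit is 12.3%. The interval is wide, and the report should show that.

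**Step 6. Which test suits sparse counts.** Take 4/43 against 0/43 as an example.

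- Expected events per arm: 4/2 = 2.
- Pearson Chi-square without correction: 86 × (4 × 43 − 39 × 0)² / (43 × 43 × 4 × 82) = 4.195, P = 0.040.
- Fisher's exact test, two-sided: 2 × C(43,4)/C(86,4) = 2 × 123,410/2,123,555 = 0.116.

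The two tests fall on opposite sides of the protocol's 0.05. With equal arms, the expected count per arm is below 5 whenever the two arms together have fewer than 10 events.

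**The case against.** The case for the protocol is substantial, and much of it stands.

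*Harms are monitored.* Adverse events and ocular examinations are scheduled at every follow-up visit, a stopping rule exists, and serious events are recorded and reported. A reader might infer that a harmed child would go unnoticed. The documents do not support that: recording is per child and carries no restriction to one eye. The gap is confined to the result that is named in advance.

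*Section 3.4 does not contradict section 6.* A reader might take the stopping rule for vision decline and central scotoma as a second contradiction. It is not one. The rule is written for unexpected serious reactions, and providing for the unexpected is compatible with a statement about what is known. The only contradiction is within section 6.

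*The wording probably meant no lasting effects.* That is likely, since the same paragraph discloses the reactions and section 7.2 says the consent form covers risks. It explains the sentence but does not make it correct.

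*Mean BCVA change is not offered as a harm detector.* This is right. It would be tempting to argue that one child's loss is diluted in the arm mean, but that holds for any mean, and the protocol never proposes this use. The left-eye point does not depend on it: a left-eye loss is absent from BCVA however BCVA is summarised.

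*The right-eye rule was meant for ocular parameters.* This is the most natural reading. BCVA is an ocular parameter, so the point survives it.

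*Tabulating harms and choosing an exact test belong to the analysis plan.* This is largely fair. The Chi-square test is named for categorical data in general, and its use for adverse events is not prescribed. Test choice matters here only because a new outcome with sparse counts would otherwise inherit that default.

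*The safety promise rests on the title alone.* This is true and limits the weight of the point, but a title that names safety still needs an outcome behind it.

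**Conclusion.** The point holds in a limited form. Section 6 makes a statement that its own next sentence refutes. The title names safety and the outcome sections designate none. The right-eye rule, as written, keeps left-eye acuity loss out of the listed outcome closest to visual harm. The primary outcome, the sample size and the collection of data are unaffected.

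The wording and designation points rest on the text alone. The illustration of 58% against 35% rests on an assumed 2% rate of one-eyed loss, equally likely in either eye; over 1% to 5% the pair runs from 35% against 19% to 89% against 66%. The 4 against 0 comparison is a chosen example, not a forecast. All figures use the enrolled 43 per arm; with the planned 20% loss, 12-month data would come from about 34, and precision would be lower. This is an inexpensive improvement that should be made, not a flaw that threatens the trial.

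**What to change.** 1. In section 6, delete the clause that claims the device has no side effects and keep the list of reactions.

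2. Add a safety outcome to section 3.5.2, built from data already scheduled: the number of children per arm with (a) any adverse event, and (b) BCVA loss of more than two lines from baseline in either eye at any follow-up visit. The threshold matches the one in section 3.4. Report (a) and (b) separately, because section 3.3 leaves subjects and clinicians unmasked and (a) depends on what they report.

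3. State in section 5 that the right-eye rule does not apply to this outcome.

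4. Report counts and denominators by arm with exact 95% confidence intervals. If a P value is given, use Fisher's exact test instead of Chi-square.

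Do not add a component for new fundus or OCT abnormalities unless a definition is supplied. A reported central scotoma would enter under (a), since section 3.6.1 schedules no visual-field test.

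The cost is a few sentences and one extra table. No new examination is needed, provided that BCVA is recorded for both eyes; the schedule does not restrict it to one. Few events are to be expected, so the intervals will be wide.
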